#### Schedule of Events

##### Clinical and Laboratory Evaluations.

The Schedule of Events listed below (Table 2) includes all study evaluations. The definitions in the following section define the evaluations, provide timelines, and include special considerations or instructions.

##### Definitions for Schedule of Events

###### Screening. Screening will generally be completed within 45 days prior to study entry.

Medical History: The Principal Investigator or his designee will perform a thorough medical history.

Complete Physical Examination: The Principal Investigator or his designee will perform a complete physical exam at the indicated times.

Tests listed below will be conducted on samples collected and analyzed by standard procedures.

If any laboratory result is outside the reference range and is considered to be clinically relevant by the Investigator, the test will be repeated at appropriate time intervals until it returns to baseline or becomes a clinically insignificant finding.

Complete Blood Count: including differential white blood cell count, absolute neutrophil count, hemoglobin and platelet count.

Hematologic Tests: PT/PTT.

Blood Chemistries: Including total electrolytes (Na, K, Cl and bicarbonate, glucose, serum BUN and creatinine, alkaline phosphatase, and albumin.

Liver Function Tests: AST, ALT and total bilirubin.

Urinalysis: Including microscopic analysis.

Viral screens: HCV antibodies, Hepatitis B surface antigen, HIV antibodies, Influenza serology.

Rheumatologic screens: ANA, RF, dsDNA.

Thyroid screens: TSH, T3, T4.

HLA haplotype: complete HLA haplotype is obtained as part of the patient database, but is not used as a clinical screening parameter. Results of HLA haplotyping do not need to be available prior to leukapheresis at week 0.

Immunologic: DTH testing to standard anergy panel, including candida, tryichophyton and tetanus.

EKG

Radiologic Tests will be performed at Memorial Sloan-Kettering Cancer Center (preferably) or New York Weill Medical College. All tests will be read by a professional radiologist and compared with prior studies whenever these are available.

Chest X-Ray: Standard PA and lateral chest X-Ray, to be completed during screening, and, for follow-up imaging during the study, within 10 days of the dates indicated in the Schedule of Events.

Bone Scan: To be completed during screening, and, for follow-up imaging during the study, within 10 days of the dates indicated in the Schedule of Events.

CT/MRI: For indicated patients, standard imaging of the abdomen and pelvis, without and with contrast, unless contrast is medically contraindicated. Either CT or MRI scans are acceptable. For follow-up imaging during the study, within 10 days of the dates indicated in the Schedule of Events.

Table 2. Schedule of Events.

Figure 1. Study flow chart.

###### On-study evaluations

Entry (Week 0)

Entry day is defined as the day of leukapheresis, which is performed 8-9 days (preferably 8 days) prior to the first immunization (which occurs on “Week 1”).

Directed History and Physical: The Principal Investigator or his designee will perform a directed history and physical, with the aim of assessing any new or unresolved signs and symptoms experienced since the last visit.

At baseline (week 0) all signs and symptoms will be recorded on the CRF. For post-baseline assessments (week 1 and subsequently), all Grade 2 or higher signs/symptoms will be recorded on the CRF. Please see Table 3 for grading of local reactions to vaccines.

Any signs or symptoms that lead to a change in treatment, regardless of grade, must be recorded on the CRFs.

Leukapheresis. All subjects in Arm 1 undergo leukapheresis at entry (“Week 0”) and all subjects in Arm 2 undergo leukapheresis at Week 0 and 8. Post treatment, all patients will undergo another leukapheresis. In the event we cannot use a leukapheresate, such as due to a poor cell yield or a contamination, the procedure may be repeated. Alternatively, in such an event, previously frozen down monocytes if available may be used to prepare the vaccine.

This procedure will be performed at The Rockefeller University GCRC.

Note: Hematology evaluations are required within 1 week prior to the leukapheresis.

100 cc of whole blood will be drawn for making autologous plasma on Week 0. White blood cells from this blood may be stored and used for additional assessment of baseline immunologic function (e.g. allogeneic mixed lymphocyte reactions, allo-MLR).

Week 1, 3, 5, 7 (Arm 1) and week 1, 3, 5, 7, 9, 11, 13, 15 (Arm 2)

History and physical, and indicated blood draws must occur prior to study vaccination.

Vaccination:

Arm 1 (up-front vaccine):

Weeks 1, 3, 5 and 7 autologous DCs co-cultured with apoptotic irradiated LNCaP cells are given SQ in single injections of 500 l. At each of these times, autologous DCs co-cultured with apoptotic irradiated LNCaP-M1 cells, as well as either saline or vaccine vehicle alone (5% DMSOin normal saline) are given SQ in single injections of 500 l. On weeks 1 and 3, autologous DCs exposed to KLH are also given SQ. The SQ injections may be given +/- 3 days from the scheduled visit, with the exception that the first injection, which will be given on day 8 (preferably) or day 9 after the patient completes leukapheresis.

Arm 2 (placebo followed by vaccine):

Weeks 1, 3, 5 and 7 Either saline or vaccine vehicle alone (5% DMSO in sterile saline) is given SQ in single injections of 500 l. At week 9, 11, 13, and 15 autologous DCs co-cultured with apoptotic irradiated LNCaP cells are given SQ in single injections of 500 l. At each of these latter times, autologous DCs co-cultured with apoptotic irradiated LNCaP-M1 cells, as well as either saline or vaccine vehicle alone (5% DMSOin normal saline ) are given SQ in single injections of 500 l. On weeks 9 and 11, autologous DCs exposed to KLH are also given SQ. The SQ injections may be given +/- 3 days from the scheduled visit, with the exception that the first injection, which will be given on day 8 (preferably) or day 9 after the patient completes leukapheresis.

Administration of Vaccine

The DC/LNCaP vaccine is given approximately 6-8 cm from the axilla in the inner aspect of the upper arm. The DC/LNCaP-M1 vaccine is given approximately 6-8 cm from the axilla in the inner aspect of the patients’ contralateral upper arm. The administration site is prepared with betadine and alcohol swabs. Injection is given with a 25-gauge needle by superficial SQ injection (not in the fatty part). DCs exposed to KLH and either saline or vaccine vehicle alone may be given in the anteromedial thigh approximately 12-24 cm distal to the inguinal ligament.

Immunologic Studies

DTH: DTH will be performed at the Rockefeller University GCRC, concurrent with each vaccination and at 2 weeks, 10 weeks and in some patients, at 22 weeks post last vaccination. DTH reactions will be read at the Rockefeller University GCRC between 40-48 hours after implantation. Results will be recorded on the CRF.

Lymphoproliferative responses, ELISPOT and CTL: Assays will be performed at the Rockefeller University.

### Outcome Parameters

#### STUDY ENDPOINTS

##### Toxicity—assessment of safety and tolerability

Toxicity will be assessed by evaluation of Grade 3 or higher adverse events, which upon review are considered to be at least possibly related to study vaccine.

All adverse events noted during the study will be tabulated by body system/organ class. All subjects will be observed in the Rockefeller University Hospital following immunizations for evidence of immediate and subacute local and systemic reactions. They will be instructed to watch for local and systemic reactions for 7 days post-immunization and will be evaluated by an investigator if significant symptoms are reported. This includes evaluation of redness, swelling and pain at the injection site and in draining lymph nodes. Objective measures will include measurement of the area of redness or swelling, and subjective measures will include self-assessment of pain on a scale of 1-10.

Systemic measures will include evaluation of fever, malaise and nausea.

Routine measurements of hematology, serum chemistry, and urinalysis laboratory tests will be performed as outlined in the Schedule of Events.

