## Broad Objectives and Planned Duration of Clinical Investigation

### Broad Objectives

There is currently no standard therapy for patients with prostate cancer who have completed conventional treatment modalities and then develop rising prostate-specific antigen (PSA) levels. We will leukapherese this group of prostate cancer patients to generate autologous dendritic cells (DCs). These will be incubated with apoptotic material from prostate cancer cell lines, and then re-introduced to the patients by subcutaneous injection to stimulate prostate tumor immune responses mediated by tumor antigen-specific killer T cells. We will monitor the patients’ immune and clinical status, including assays to determine whether this protocol leads to any adverse allergic or autoimmune reaction. To determine that the immunization was active, we will monitor delayed type hypersensitivity (DTH) skin tests. As an additional assay for the activity of our vaccine approach, patients will also be immunized with DCs that have been co-cultured with prostate tumor cell lines stably transfected with the influenza matrix antigen (LNCaP-M1 cells). This will allow us to monitor responses to a built-in “positive control” antigen by examining T cell reactivity to the influenza matrix antigen. By determining vaccine activity, we will be able to make robust conclusions regarding vaccine toxicity.

To help control for events related to the natural history of prostate cancer patients during the course of the trial, half of our patients will randomly be placed into a placebo arm of the study, in which they will receive either saline or the vaccine vehicle only injections (5% DMSO in sterile saline) subcutaneously during the first 8 weeks of the trial, and then cross-over to be immunized on a schedule identical to patients who receive the autologous DC vaccine up front. This trial design will aid us in assessing whether adverse events are treatment related in our cohort of cancer patients.

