### Study Design

Phase I/II prospective randomized, single-blinded, placebo-controlled trial with 2 arms describing the toxicity and activity of immunization with DC-LNCaP. Study participants in Arm 2, but not the investigator, study personnel, or those study participants in Arm 1 will be blinded with respect to up-front treatment (vaccine or placebo). At week 8, all patients will be made aware of which treatment arm they are in.

Arm 1. Subcutaneous injection of *ex vivo* generated autologous dendritic cells pulsed with apoptotic LNCaP cells, pulsed with apoptotic LNCaP-M1 cells (control apoptotic cells) and pulsed with KLH (control antigen). In addition, subcutaneous injection of either saline or vaccine vehicle only (5% DMSO in normal saline ).

Arm 2. Subcutaneous injection of either saline or vaccine vehicle only (5% DMSO in normal saline ), followed by cross-over to Arm 1 design.

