#### Biostatistical analysis.

The primary specific aim is to compare the clinical status during the first part of the study (before the cross-over) between the placebo and the vaccine group. As defined in CFR, Phase-I/II studies should address both acute toxicity and activity/efficacy. Accordingly, this comparison will be based on two primary outcomes:

(1) activity: relative change in PSA.

We do not use the term “efficacy” here, because we recognize that change in PSA is not a validated “surrogate” for clinical benefit. The primary manifestations of disease progression in prostate cancer are rising PSA values, new lesions on bone scan, new symptoms of disease, and, less frequently, an increase in measurable tumor mass. Several groups have shown the prognostic significance of post-therapy declines in PSA, leading to an NCI consensus group proposal of a set of guidelines for the use of post-therapy PSA that can be used in phase II trials to identify agents for further testing (Fazzari et al., 2000).

(2) acute toxicity: incidence and severity of an adverse events.

Although the variables will be combined to address the overall clinical status, the power calculations below address each of these aspects independently.

Size of relevant differences: For activity, we would like to have sufficient power to detect a 50% decline in PSA in the treatment group vs. no change in the placebo group. For toxicity, we would like to have sufficient power to detect a 50% incidence of severe adverse events (acute toxicity) vs. a 5% incidence.

Power vs. level: If there should be acute toxicity, we do not want to overlook this (false negative result). A similar argument holds for activity: as long as the treatment with apoptotic LNCaP-DCs is well tolerated, we would rather go on with the next trial, even if we would later find out that apoptotic LNCaP-DCs are not active (false positive result), than to risk delaying the development of an effective treatment (false negative result). Thus, we want to guarantee 90% power for the above differences at the 10% level. If we should see lower acute toxicity in the vaccine group (unlikely) or higher activity in the placebo group (also unlikely), our decision would be the same as if we would see no difference: we would reconsider the use of this vaccination in the treatment of advanced prostate cancer. Given this one-sided decision strategy we will further increase power by using one-sided tests.

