Benefit: For the final analysis, PSA markers and adverse event indicators will be combined to assess the overall benefit of the vaccination. We will compute marginal likelihood scores (Susser et al., 1998) based on the relative change in PSA and the highest adverse event category observed in each patient. SAEs will "overwrite" any benefit of the vaccination, while other adverse events will augment the benefit. Thus, if large declines in PSA are observed in patients with more adverse events, the overall benefit of the vaccination will be downgraded. On the other hand, if adverse events are predominantly observed among patients with increase in PSA, this strategy increases power.

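### The toxicity endpoint is defined in two unreconciled ways, one of them resting on unblinded attribution, and the benefit score contradicts itself on non-serious adverse events

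*Combined protocol and SAP*

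**What the plan says.** Under Study Endpoints, the section on toxicity assesses adverse events of Grade 3 or above "which upon review are considered to be at least possibly related to study vaccine". The Vaccine Toxicity section gives the relatedness judgement to the investigator. On masking, Study Design states: "Study participants in Arm 2, but not the investigator, study personnel, or those study participants in Arm 1 will be blinded". Broad Objectives gives the reason for having a placebo phase: "This trial design will aid us in assessing whether adverse events are treatment related in our cohort of cancer patients".

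Other parts of the plan apply no relatedness filter. The same endpoint section adds: "All adverse events noted during the study will be tabulated by body system/organ class". Biostatistical analysis names the second primary outcome as "acute toxicity: incidence and severity of an adverse events", to be compared between arms before the cross-over. It then states the target difference in terms of severe events, and the Fisher test, the power and the comparative stopping rule in terms of SAEs. The Serious Adverse Events section defines 'serious' by outcome (death, threat to life, disability, hospitalization) and uses 'severe' for CTC Grade 3.

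The Benefit paragraph combines PSA change with each patient's highest adverse event category. SAEs cancel any benefit, "while other adverse events will augment the benefit". The following sentence says that PSA falls accompanied by more adverse events lower the overall benefit.

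**The concern.** Toxicity is one of two primary outcomes, yet the plan does not say whether the endpoint section or the statistical section decides which events are compared. The two versions behave differently. Before crossover an Arm 2 patient has received no cells, so an investigator who knows this has little basis for calling an event vaccine-related. Filtering on relatedness first presumes the answer that the placebo phase was meant to supply. Depending on how freely vaccine-arm events are attributed, background illness could appear as toxicity, or real toxicity could be diluted.

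The severe/serious wording adds a second ambiguity, because a Grade 3 event need not be serious.

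The Benefit paragraph raises a separate problem in the final analysis. Taken literally, one clause rewards non-serious toxicity, and no scoring program can satisfy both that clause and the sentence after it.

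**Working it through.** **Definitions side by side**

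| Place | What counts | Relatedness filter |
|---|---|---|
| Study Endpoints, toxicity | Grade 3+ events | Yes, at least possible |
| Same section, tabulation | All adverse events | None |
| Biostatistical analysis, primary outcome 2 | Incidence and severity of adverse events | None |
| Biostatistical analysis, target difference | Severe events, 5% v 50% | None |
| Biostatistical analysis, Fisher test, power, comparative stopping rule | SAEs (once called severe for the same counts) | None |
| Biostatistical analysis, Benefit | Highest adverse event category; SAEs override | None |

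**Inputs.** From Biostatistical analysis: 12 per arm, one-sided Fisher exact test, 10% level, 5% v 50%. Background rates above 5% and all attribution shares are my assumptions; the documents give neither.

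**The plan's own figures.** The one-sided exact p-value for 3 v 0 is C(12,3)/C(24,3) = 220/2024 = 0.109. For 4 v 1 it is 0.158 and for 5 v 1 it is 0.077. All three match. The stated 90% power for 5% v 50% reproduces with a normal approximation (91.5%). Full enumeration of the named Fisher test gives 84.0%, which is the baseline used here; that gap is a separate matter.

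**Putting the attributed endpoint into the test.** Let b be the true event rate, and q_V and q_P the shares called related in the vaccine and placebo arms. The counts are then Binomial(12, b·q_V) and Binomial(12, b·q_P). With q_P = 0 the placebo count is always 0. The test then rejects at four or more vaccine-arm patients, because 4 v 0 gives 495/10626 = 0.047 while 3 v 0 gives 0.109. The rejection probability is therefore P(Binomial(12, b·q_V) ≥ 4).

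Example with b = 20% in both arms and q_V = 1: 1 − (0.0687 + 0.2062 + 0.2835 + 0.2362) = 1 − 0.7946 = 20.5%.

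False-positive rate when both arms have the same true rate:

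| True rate | All-cause | 100%/0% | 75%/0% | 50%/0% |
|---|---|---|---|---|
| 5% | 0.1% | 0.2% | 0.1% | 0.0% |
| 10% | 0.9% | 2.6% | 1.0% | 0.2% |
| 20% | 3.5% | 20.5% | 9.2% | 2.6% |
| 30% | 4.9% | 50.7% | 27.6% | 9.2% |

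Power when the truth is 5% v 50%: 84.0% on all-cause counts, 92.7% at 100%/0%, 71.8% at 75%/0%, and 35.1% at 50%/0%. The last is P(Binomial(12, 0.25) ≥ 4) = 1 − (0.0317 + 0.1267 + 0.2323 + 0.2581) = 1 − 0.6488.

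**Direction of the benefit score.** The Benefit paragraph makes four statements about adverse events:

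1. An SAE cancels any PSA benefit (unfavourable).
2. Other adverse events augment benefit (favourable).
3. PSA falls paired with more adverse events lower the overall benefit (unfavourable).
4. Power rises if adverse events fall mainly on patients whose PSA increases (consistent with unfavourable).

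Take two patients with the same large PSA fall and no SAE, one of whom has a Grade 2 event. Statement 2 scores that patient higher and statement 3 scores him lower.

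**The case against.** The strongest reply is that the formal analysis already does the right thing. The Fisher test, the power figures, the comparative stopping rule, the adverse event tabulation and the combined score carry no relatedness filter. A reader might infer that the placebo arm is lost as a control. The documents do not support that, because the planned SAE comparison uses counts from both arms. For events reported at inpatient visits, a hospitalist also decides seriousness, in a process separate from the investigator's. That stands, although it concerns seriousness and not relatedness.

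The larger error rates rest on assumptions. The plan takes 5% as the placebo rate, and entry requires Karnofsky 70-100% and a life expectancy of at least one year. At 5% background even extreme attribution gives 0.2%. Zero attribution in the placebo arm is not automatic: placebo may be the vaccine vehicle, and the attribution scale refers to the study drug or investigational agent. If all vaccine-arm events and half of placebo events were called related, a 20% background would give 9.0%, inside the 10% level. So the 20.5% and 50.7% figures are scenarios, not the trial's expected error rate.

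A reader might also infer that the benefit score runs backwards. That is not shown. Three of its four statements treat adverse events as unfavourable, so the paragraph is self-contradictory and its evident intent is the usual one.

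What the reply does not remove is that the attributed version is the one printed under Study Endpoints, and nothing says the statistical section overrides it.

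**Conclusion.** The point holds as an inconsistency in a primary outcome and a contradiction in the final combined analysis. Toxicity is defined both as related Grade 3+ events, attributed by an unblinded investigator, and as unfiltered adverse events or SAEs, with 'severe' and 'serious' not kept apart. The consequence is conditional: it arises only if the attributed version is the one tested. It is then negligible for false positives at the plan's 5% background, large at assumed backgrounds of 20-30% with one-sided attribution, and able to hide real harm when vaccine-arm events are under-attributed. The 'augment' clause needs correcting whichever endpoint is chosen.

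**What to change.** - In the endpoint section, name all-cause events in both arms, over the same pre-crossover window, as the comparative toxicity endpoint, in line with Biostatistical analysis.
- State whether that endpoint is SAEs as defined under Serious Adverse Events or Grade 3+ events, and use that term throughout. If Grade 3+ is chosen, the power statement and illustrative p-values, now worded for SAEs, need restating in that term.
- Keep attribution as a descriptive column in the tabulation.
- In the Benefit paragraph, replace 'augment' with 'reduce'. Keep the rule that an SAE overrides any PSA benefit, and write out the resulting ordering so that it can be programmed.

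The cost is a protocol and SAP wording change before analysis. No new data are needed, since the adverse event log already records grade and attribution for each event. The small downside is that background events add some noise to both arms.

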##### Activity

Activity of vaccination will be measure by monitoring both clinical and immunologic parameters. The primary clinical parameter of activity will be PSA measurement. Secondary clinical parameters include monitoring of measurable disease, assessed by chest X-Ray, bone scan and CT scan/MRI scans.

PSA will be measured in the MSKCC laboratory and serially monitored starting at the screening visit, Day 0, Week 3, 4, 5, 7, 9, 13, and 17, (and possibly 29) for participants in Arm 1 and on screening visit, Week 3, 4, 5, 6, 7, 9, 11, 12, 13, 15, 17, 21, and 25, (and possibly 37) for participants in Arm 2.

Complete response (CR): PSA < 4.0 ng/ml for 3 successive evaluations at least two weeks apart.

Partial Response (PR): Decrease in PSA value by > 50% (without normalization) for three successive evaluations at least two weeks apart.

Stabilization (SD): Patients who do not meet the criteria for PR or PD for at least 90 days on study (post vaccine; week 1 (Arm 1) or week 10 (Arm 2)).

Progression (PD): Three consecutive increase in PSA from baseline or nadir, each measurement at least two weeks apart.

Time to PSA Progression: The first PSA rise after the nadir PSA that is confirmed by two consecutive PSA at least two weeks or more apart.

Measurable disease

Patients will be evaluated at baseline, and at 5 weeks and 17 weeks after completion of therapy. Response and progression of measurable disease will be evaluated by bone scan and soft-tissue CT scan, using criteria proposed by the Response Evaluation Criteria in Solid Tumors (RECIST) Committee (Therasse et al., 2000). Changes in only the largest diameter (uni-dimensional measurement) of the tumor lesions are used in the RECIST criteria. Note: Lesions are either measurable or non-measurable using the criteria provided below.

Measurable disease: Defined as lesions that can be accurately measured in at least one dimension (longest diameter to be recorded) as >20 mm with conventional techniques (PET, CT, MRI, x-ray) or as >10 mm with spiral CT scan.

Non-measurable disease: All other lesions, including small lesions, are considered non-measurable disease. Bone lesions, leptomeningeal disease, ascites, plueral/pericardial effusions, lymphangitic disease, inflammatory disease are all non-measurable.

Target lesions: All measurable lesions up to a maximum of five per organ and 10 in total representative of all involved organs should be identified as target lesions and recorded and measured at baseline. Target lesions should be selected on the basis of their size (lesions with the longest diameter) and their suitability for accurate repeated measurements (either by imaging techniques or clinically). A sum of the longest diameter (LD) for all target lesions will be calculated and reported as the baseline sum LD, which will serve as a reference by which to characterize tumor response.

Non-target lesions: All other lesions should be identified as non-target lesions and should also be recorded at baseline. Non-target lesions include measurable lesions that exceed the maximum numbers per organ or total of all involved organs as well as non-measurable lesions. Measurements of these lesions are not required, but the presence or absence of each should be noted throughout follow-up.

Guidelines for evaluation of measurable disease: All measurements should be taken and recorded in metric notation using a ruler or calipers. All baseline evaluations should be performed as closely as possible to the beginning of treatment and never more than 4 weeks before the beginning of the treatment. Tumor lesions that are situated in a previously irradiated area are not considered measurable. The same method of assessment and the same technique should be used to characterize each identified and reported lesion at baseline and during follow-up. Imaging-based evaluation is preferred to evaluation by clinical examination when both methods have been used to assess the antitumor effect of a treatment.

Radionuclide bone scan

Subjectivity in interpreting serial changes in radionuclide bone scan is well recognized. Thus the primary outcome will be whether the scan is stable or improved, vs. worse or progression. Changes in intensity will not be used as an outcome measure.

Stable or improved: Requires that no new lesions appear, or that new pain has not developed in an area that was previously visualized.

Progression (Non-response): New areas of focal uptake.

Time to Progression: Time to progression will be defined as the time from the first day of treatment with vaccine until the date PD or death is first reported. Patients who die without a reported prior progression will be considered to have progressed on the day of their death.

Chest x-ray

Lesions on chest x-ray are acceptable as measurable lesions when they are clearly defined and surrounded by aerated lung. However, CT is preferable.

CT and MRI

These techniques should be performed with cuts of 10mm or less in slice thickness contiguously. Spiral CT should be performed using a 5 mm contiguous reconstruction algorithm. This applies to tumors of the chest, abdomen, and pelvis. Head and neck tumors and those of extremities usually require specific protocols.

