##### --Disease Characteristics--

1. Histologically confirmed prostate carcinoma

2. Progressive, disease required, i.e.: elevated PSA documented to be rising on 3 occasions, either despite castrate testosterone levels (below 50 ng/dl), or after definitive local therapy (prostatectomy or radiation).

| Extent of disease | Min # of values | Interval |
| --- | --- | --- |
| Rising PSA within 2 years of prostatectomy | 3 | >2 weeks |
| Rising PSA post-radiation* | 3 | >2 weeks |
| Rising PSA despite castrate testosterone | 3 | >2 weeks |

*Baseline is defined as the first of three rising values confirmed after definitive radiation treatment.

3. No active CNS metastases

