##### --Prior/Concurrent Therapy--

1. Recovered from toxicity of any prior therapy

2. Biologic therapy:

No prior autologous or allogeneic tumor vaccines

No concurrent other immunotherapy

3. Chemotherapy:

At least 4 weeks since chemotherapy

Not previously treated with more than 2 chemotherapy regimens

No concurrent chemotherapy

4. Endocrine evaluation/therapy:

3 rising PSA values at least 2 weeks apart

At least 2 weeks since concurrent corticosteroids (other than for replacement therapy for adrenal insufficiency)

Medical hormonal therapy to maintain castrate testosterone levels permitted

5. Radiotherapy:

At least 4 weeks since radiotherapy

No concurrent radiotherapy

6. Surgery:

Prior surgery allowed

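### The PSA complete-response rule is a fixed level with no required fall, and entry sets no PSA minimum, so a man with low, rising PSA can be CR and PD at once; only the descriptive response categories are affected.

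*Combined protocol and SAP*

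**What the plan says.** **Response categories (Outcome Parameters, Activity).**
- Complete response (CR): "Complete response (CR): PSA < 4.0 ng/ml for 3 successive evaluations at least two weeks apart". The rule names no baseline, asks for no decline and gives no date from which evaluations count.
- Partial response (PR): "Decrease in PSA value by > 50% (without normalization) for three successive evaluations at least two weeks apart".
- Progression (PD): "Three consecutive increase in PSA from baseline or nadir, each measurement at least two weeks apart".
- Stabilization (SD): "Patients who do not meet the criteria for PR or PD for at least 90 days on study". CR is not among the exclusions.
- No order of precedence is given.

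**Entry PSA.** Disease Characteristics requires "elevated PSA documented to be rising on 3 occasions, either despite castrate testosterone levels (below 50 ng/dl), or after definitive local therapy". The table beneath it sets only the number and spacing of values; its surgical row reads "Rising PSA within 2 years of prostatectomy". Prior/Concurrent Therapy repeats the requirement as "3 rising PSA values at least 2 weeks apart". Elevated is never given a number.

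**Where PSA enters the analysis.** Biostatistical analysis makes relative change in PSA the primary activity outcome, compared between arms before the cross-over by a Wilcoxon-Mann-Whitney test. The combined benefit score also uses relative change in PSA. Neither refers to CR, PR, SD or PD.

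**The concern.** A response category should record a change after treatment. This CR rule records where the PSA sits. PR, one line below it, does require a fall, so the higher category asks for less evidence of effect than the lower one.

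If men can enter below 4.0 ng/ml, some will satisfy CR because of who they are and not because of what the vaccine did. Some of them will satisfy PD on the same values. With no precedence rule, the label would be chosen after the data are seen. Any reported CR proportion would then mix vaccine activity with the share of low-PSA men enrolled.

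**Working it through.** The plan states no CR rate or CR-based sample size, so there is no figure to reproduce. The check applies the rules literally to a PSA that only rises.

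**Inputs from the protocol.** CR, PR and PD as above. Arm 1 PSA at Day 0 and weeks 3, 4, 5, 7, 9, 13 and 17. Weeks 3, 5 and 7 give three evaluations two weeks apart.

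**Assumptions.** Entry PSA *B* and doubling time are not in the documents, so a range is used. Growth is exponential: PSA(w) = B × 2^(w/D), with D = doubling time in months × 52/12 weeks. Thus 3 months = 13 weeks and 6 months = 26 weeks.

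**Step 1: worked patients.**

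| Entry PSA | Doubling time | Week 3 | Week 5 | Week 7 | CR | PR | PD |
|---|---|---|---|---|---|---|---|
| 1.0 | 6 months | 1.08 | 1.14 | 1.21 | yes | no | yes |
| 2.0 | 3 months | 2.35 | 2.61 | 2.90 | yes | no | yes |
| 3.0 | 6 months | 3.25 | 3.43 | 3.62 | yes | no | yes |
| 3.0 | 3 months | 3.52 | 3.92 | 4.36 | no | no | yes |

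PD is met because Day 0, week 3, week 5 and week 7 give three consecutive increases.

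**Step 2: highest entry PSA that still gives CR by week 7.** On a rising curve only the last value binds, so B < 4 / 2^(7/D).
- 3 months: 4 / 2^(7/13) = 2.75 ng/ml.
- 6 months: 4 / 2^(7/26) = 3.32 ng/ml.
- 2 and 12 months, as outer limits: 2.29 and 3.64 ng/ml.

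If successive means adjacent scheduled draws with none skipped, Arm 1's first qualifying run after vaccination is weeks 5, 7 and 9. The ceilings become 4 / 2^(9/13) = 2.48 and 4 / 2^(9/26) = 3.15 ng/ml. The conclusion does not depend on that reading.

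**Step 3: Arm 2.** Its PSA list also has weeks 3, 5 and 7, all before the first vaccine at week 9. Counting spaced evaluations, a man can meet CR on placebo. On the adjacent-draw reading the first on-study run is weeks 7, 9 and 11, which straddles the change to vaccine.

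**Step 4: other literal results.**
- A sustained fall from 4.1 to 3.9 is CR: (4.1 − 3.9)/4.1 = 4.9%.
- A fall from 20 to 9, (20 − 9)/20 = 55%, is only PR.
- If normalization means below 4.0, a fall from 3.0 to 1.2 (60%) is CR, the same label as the man rising from 1.0 to 1.21.
- A man flat at 3.0 for 90 days is both CR and SD.

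**Step 5: size.** If the vaccine does nothing, the false-CR proportion is the share of men who enter low enough. The documents do not give that share. For illustration, 3, 6 or 12 of 24 would be 12.5%, 25% or 50%.

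**The case against.** The best defence is the word elevated in the entry criterion. PR excludes normalization and sits beside a CR cut-off of 4.0, which suggests that CR was meant as the return of a raised value to normal. The sample-size text likewise supposes that placebo PSA stays elevated or increases in at least two-thirds of patients. If elevated means 4.0 or above, no one enters below the cut-off and the CR-with-PD case does not arise from entry. That reading is plausible, but the documents never state it, and the table rows ask only for rising values. It would also leave the 4.1-to-3.9 case and the overlap of CR with SD.

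The second defence is that no planned test uses CR, and this stands in full. A reader might infer that the activity comparison is compromised. It is not: a man whose PSA rises from a low value is ranked as a rise in the primary test and enters the benefit score as a rise. The sample size does not rest on CR. Randomisation is 1:1, so low-PSA false responders would be expected in both arms, and the comparison before cross-over is not systematically biased.

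**Conclusion.** The defect is real but confined to the descriptive CR/PR/SD/PD classification. As written, CR needs no fall, entry has no numeric PSA minimum, and CR can coincide with PD or SD with no rule to decide between them. With assumed doubling times of 3 and 6 months, rising patients can be CR by week 7 from entry values up to about 2.75 and 3.3 ng/ml. This rests on elevated not meaning 4.0 or more.

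Two stronger readings are not supported. One is that every man entering below 4.0 becomes a complete responder: entry at 3.0 with a 3-month doubling time does not, and a rising PSA that starts at or above 4.0 never does. The other is that an inert vaccine would show some particular CR rate, such as 25%. That figure only restates an assumed 6 of 24; the plan gives no entry PSA distribution and schedules no CR-rate analysis. The point is worth correcting before data are seen, chiefly so that labels are not chosen afterwards.

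**What to change.** Amend the Activity definitions as follows.

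1. **CR.** Allow it only when a named baseline PSA is at least 4.0 ng/ml. Require a confirmed fall of more than 50% from that baseline as well as values below 4.0 on three spaced evaluations. This uses the plan's own PR threshold, so CR becomes a subset of PR-size declines.
2. **Baseline below 4.0.** Classify by percent change only, and drop the normalization exclusion from PR for these men.
3. **Name the baseline.** Use Day 0 for Arm 1. Use screening for Arm 2's placebo phase, because the Activity section lists no Day 0 PSA for that arm. Use the last pre-vaccine PSA (week 9) for Arm 2's vaccine phase, reconciled with the week 10 start given in the SD definition.
4. **Start of counting.** Count vaccine-phase response only from evaluations after the first vaccine dose.
5. **Mutually exclusive categories.** SD also excludes CR. Rising values that never fell from baseline are PD, not CR. A rise after a confirmed response is recorded as later progression and does not erase the response.
6. **State what elevated means** at entry. On its own this would not be enough, for the reasons given under the objection.

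The cost is wording only, with no added visits, draws or patients. The downside is that fewer patients are evaluable for CR. A man who falls below 4.0 by 50% or less, for example from 6.0 to 3.5 (2.5/6.0 = 42%), is then not a responder.
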